# Study of Optimal Replacement of Thyroxine in the ElDerly (SORTED): protocol for a mixed methods feasibility study to assess the clinical utility of lower dose thyroxine in elderly hypothyroid patients: study protocol for a randomized controlled trial

**DOI:** 10.1186/1745-6215-14-83

**Published:** 2013-03-22

**Keywords:** Hypothyroidism, Ageing, General practice, Primary health care, Cardiovascular disease, Thyroxine, Feasibility, Randomized controlled trial

## Abstract

**Background:**

The population of the UK is ageing. There is compelling evidence that thyroid stimulating hormone distribution levels increase with age. Currently, in UK clinical practice elderly hypothyroid patients are treated with levothyroxine to lower their thyroid stimulating hormone levels to a standard non-age-related range. Evidence suggests that mortality is negatively associated with thyroid stimulating hormone levels. We report the protocol of a feasibility study working towards a full-scale randomized controlled trial to test whether lower dose levothyroxine has beneficial cardiovascular outcomes in the oldest old.

**Methods/design:**

SORTED is a mixed methods study with three components:

SORTED A: A feasibility study of a dual-center single-blinded randomized controlled trial of elderly hypothyroid patients currently treated with levothyroxine.

Setting: Patients will be recruited from 20 general practices and two hospital trust endocrine units in Northumberland, Tyne and Wear.

Participants: Target recruitment of 50 elderly hypothyroid patients currently treated with levothyroxine, identified in both primary and secondary care settings.

Intervention: Reduced dose of levothyroxine to achieve an elevated serum thyroid stimulating hormone (target range 4.1 to 8.0 mU/L) versus standard levothyroxine replacement (target range 0.4 to 4.0 mU/L).

Randomization: Using random permuted blocks, in a ratio of 1:1, randomization will be carried out by Newcastle Clinical Trials Unit.

Outcomes: Study feasibility (recruitment and retention rates and medication compliance), acceptability of the trial design, assessment of mobility and falls risk, and change in cardiovascular risk factors.

SORTED B: Qualitative study using in-depth interviews to understand patients’ willingness to take part in a randomized controlled trial and participants’ experience of the intervention.

SORTED C: Retrospective cohort study of 400 treated hypothyroid patients aged 80 years or over registered in 2008 in primary care practices, studying their 4-year cardiovascular outcomes to inform the power of SORTED II.

**Discussion:**

This is a study to evaluate the feasibility of conducting a randomized controlled trial in elderly hypothyroid patients in general practice and hospital settings. The results will inform the design of the definitive SORTED II trial to evaluate the effects of lower dose thyroxine in elderly hypothyroid patients.

**Trial registration:**

Current Controlled Trials http://ISRCTN16043724

## Background

The population of the UK is ageing. Over the last 25 years the percentage of the population aged 65 and over increased from 15% in 1984 to 16% in 2009, an increase of 1.7 million people. Over the same period, the percentage of the population aged under 16 decreased from 21% to 19%. This trend is projected to continue. By 2034, 23% of the population is projected to be aged 65 and over compared to 18% aged under 16.

The greatest population increase has been in the number of those aged 85 and over, the ‘oldest old’. In 1984, there were around 660,000 people in the UK aged 85 and over. Since then the numbers have more than doubled reaching 1.4 million in 2009. By 2034 the number of people aged 85 and over is projected to be 2.5 times larger than in 2009, reaching 3.5 million and accounting for 5% of the total population [1].

Thyroid hormones are crucial in controlling metabolism and have an impact on a wide array of tissues including brain, heart, muscle and bones. Thyroid dysfunction is common, affecting all age groups, with a higher frequency in women and older individuals. In the NHANES III survey, a study designed to provide normative estimates of health and nutritional parameters in the USA, a raised serum thyroid stimulating hormone (TSH) level (>4.5 mU/L) was found in 14% of the population aged 80 years or over [2]. In the UK, the population-based Whickham study found that 10% of the population over the age of 75 years had a raised TSH level (>6.0 mU/L) [3]. There is compelling evidence that serum TSH distribution levels increase progressively with age in the reference population with the 97.5th centile being 4.03 mU/L in the 50 to 59 age group and 7.49 mU/L in the 80+ age group [4]. Therefore the prevalence of hypothyroidism and subclinical hypothyroidism is likely to be significantly overestimated in the oldest old and, more importantly, treatment with levothyroxine (LT4) inappropriately initiated in a proportion of these.

Treating elderly patients who have mildly elevated TSH with LT4 does not improve cognitive function [5]. It is recognized that over-treatment with thyroid hormones has the potential for deleterious effects on quality of life, skeletal health, cardiovascular mortality and incidence of atrial fibrillation [6]. This finding has been borne out in the well-designed prospective follow-up study of 85-year-old individuals in Leiden [7]. This study showed that mortality was negatively associated with TSH levels and increased with higher free thyroxine levels. Furthermore, in the same study, subgroup analyses after exclusion of individuals on medication for thyroid disease showed that higher TSH and lower thyroxine levels were associated with reduced worsening of disability, better memory and reduced mortality over 4 years of follow-up. In another study of older untreated adults aged more than 70 years, a mildly elevated TSH between 4.5 and 7.0 mU/L was associated with a slight functional advantage in mobility compared to those with TSH levels of 0.4 to 4.5 mU/L [8]. This suggests that treatment with thyroid hormones could worsen these important outcomes in elderly individuals. Another study of older women (>65 years) found that mortality in thyroid hormone users tended to be higher with a hazard ratio (95% CI) of 1.11 (0.98 to 1.24) and that mildly elevated TSH was not associated with excess cardiovascular mortality [9]. A meta-analysis of observational population-based studies [10], and confirmed by others [11], has shown that mild hypothyroidism in the elderly is not hazardous for vascular mortality and events.

Currently, all individuals with hypothyroidism are treated as a homogenous group irrespective of age with the aim of achieving serum TSH levels within the reference range (0.4 to 4.0 mU/L). However, thyroxine metabolism is altered in advanced age, and ‘age-adjusted’ reference ranges are not employed [12]. Experts suggest that in older hypothyroid patients LT4 treatment should be tailored to have a higher ‘target’ TSH value compared to younger individuals and that ‘prospective therapeutic trials are necessary to clarify the necessity of replacement therapy in the elderly’ [6]. There is neither consensus nor published NICE clinical guidelines to help clinicians manage mild hypothyroidism or subclinical hypothyroidism in older patients. This presents a significant problem for general practitioners (GPs), who manage the majority of these patients [13]. It is imperative to gather evidence and determine whether they should be treated with a more appropriate TSH target, and whether this improves overall as well as cardiovascular morbidity and mortality.

### The future definitive trial: SORTED II

The objective of SORTED II is to address the question of whether elderly hypothyroid patients maintained with a slightly higher TSH reference range, have better morbidity, mortality and cardiovascular outcomes, compared with current usual treatment. Where the feasibility, patient acceptability and parameters to inform a power calculation are lacking for a definitive trial, a well-designed feasibility study is required [14]. In the SORTED study we will test protocol procedures, patient recruitment and retention rates, consent processes, randomization, patient acceptability, and collect data to power SORTED II. This paper describes the three components of the protocol for the feasibility study SORTED, a necessary precursor to SORTED II.

## Methods/design

### Aim: SORTED (A, B and C)

The aim of this study is to explore the design, patient acceptability and required sample size to power the definitive SORTED II trial adequately. Specifically we aim to provide evidence that it is feasible to perform a large randomized controlled trial (RCT) assessing lower dose LT4 in treated elderly hypothyroid patients, evaluating the participants’ experience in the trial as well as morbidity and mortality rates over 4 years in a cohort of patients in general practice.

### SORTED A: RCT feasibility study

#### Aim

The aim is to assess participants’ willingness to enter and complete a single-blinded randomized controlled trial of lower dose thyroxine for elderly hypothyroid patients.

#### Primary objectives

The primary objectives are to show that recruitment to such a trial is possible; to gauge participants’ acceptability of being part of the study; to assess the length of time required to complete recruitment; to assess the dose titration strategy and the length of time required to achieve desired TSH levels; and to gauge medication compliance.

#### Secondary objectives

The secondary objectives are to measure the acceptability and usefulness of generic and validated disease-specific quality of life questionnaires, EQ-5D [15], ThyDQoL and ThySRQ [16]; to assess mobility and risk of falls in this population group as measured by the TUG test and FRAT questionnaire [17]; and to measure changes in specific cardiovascular risk factors including lipid profile, blood pressure and body weight and changes in bone resorption markers.

#### Design

This is a feasibility study for a dual-center single-blinded RCT of elderly hypothyroid patients currently treated with LT4. It is a clinical trial of an investigational medicinal product. The study will compare the standard dose of LT4 (target TSH level 0.4 to 4.0 mU/L) with a lower dose of LT4 (target TSH levels 4.1 to 8.0 mU/L), until TSH is within the desired range. Post randomization, individuals will be assessed at 12 weeks (and LT4 dose adjusted) and at 24 weeks, with a final follow-up phone call at 25 weeks.

#### Study setting and population

Patients will be recruited from 20 research general practices that are supported by the National Institute for Health Research (NIHR), and two hospital trust endocrine units in Northumberland, Tyne and Wear. The study population comprises elderly hypothyroid patients currently treated with LT4.

#### Inclusion criteria

Males and females aged 80 years or over are included if:

• They have been diagnosed with hypothyroidism and treated with LT4 for at least 6 months.

• They are living independently in the community.

• All of their TSH results are within the range 0.4 to 4 mU/L in the 3 months before commencing the study.

• They have provided written informed consent for participation in the study, prior to any study-specific procedures.

#### Exclusion criteria

People are excluded if:

• They have established dementia and therefore deemed incapable of providing informed consent.

• They have other medical conditions, which, in the opinion of the chief investigator, would prevent them from taking part in the study (for example, end stage cancer or severe chronic health conditions where the patient is housebound).

• They are a resident of a nursing home or residential care home.

• They have with thyroid cancer, as they would require high doses of LT4 to suppress their serum TSH.

• They take 25 mcg of LT4 daily: dose reduction will mean that they stop thyroid replacement treatment.

• They do not speak English.

• They have participated in any other investigational trials within the last 3 months.

• They have been prescribed medications that can affect thyroid function (amiodarone, lithium, carbimazole or propylthiouracil).

• They have known or suspected lactose intolerance (this would have implications for the proposed over-encapsulated investigational medicinal product (IMP)).

#### Screening, recruitment and consent

Three methods of recruitment will be adopted for the RCT feasibility study: via a database search of GP practices, opportunistically via secondary care clinics and via poster advertising and self-referral.

Firstly, general practices will act as participant identification centers (PICs) and practice staff will perform a database search using a protocol eligibility criteria flow chart, which simultaneously identifies the SORTED C cohort and potential SORTED A participants (Figure 1). The NIHR Primary Care Research Network team will provide the central study team with a completed eligibility proforma for each potential participant (identified by a unique patient number only). The proforma will be a checklist of all inclusion and exclusion criteria to confirm each participant meets all eligibility criteria. The GP will review the list of eligible SORTED A participants. The practice will approach potential participants by posting a study invitation pack to their home address within 2 working days of the database search.

**Figure 1 F1:**
[figure not shown]
**Search flow chart for the simultaneous retrieval of retrospective cohort data and trial participant data.** For the RCT we need patients with hypothyroidism and who were ≥80 years old in 2012. For the retrospective cohort study we need patients with a diagnosis of hypothyroidism who were ≥80 years old in 2008, and followed up (alive and dead) until 2012. RCT: randomized controlled trial.

Secondly, potential participants in secondary care will be identified and invited to participate during routine endocrine clinic visits at the Gateshead Health NHS Foundation Trust and the Newcastle upon Tyne Hospitals NHS Foundation Trust. The initial approach in the clinic will be via the clinician in charge of their routine clinical care. A brief verbal explanation of the study will be provided by the clinician and the participant will be given a study invitation pack.

Finally, we will use study posters in non-research active practices in and around the Northumberland and Tyne and Wear area. Potential participants can contact the central study team directly. The central study team will assess the eligibility criteria then send a study invitation pack.

Potential participants will receive a study invitation pack consisting of:

• Either a pre-prepared invitation letter from the general practice, an invitation letter from their routine clinician in secondary care, or an invitation letter from the central study team in response to a poster enquiry.

• A participant information sheet and consent form.

• A stamped addressed envelope to return the reply slip to the central study team.

On receipt of the reply slip, the central study team will contact potential participants by telephone 7 (+/− 3) days later to confirm the patient’s interest in participating, answer any initial questions and arrange a convenient date and time for the screening visit. If potential participants are not contactable by telephone, then a home visit appointment will be arranged by letter to discuss this information.

If no reply slip is received by the central study team within 4 weeks, a reminder will be sent to the patient’s home address within 2 working days. The reminder will also contain an invitation pack for SORTED B Group 2 (see below) to minimize the number of approaches to each particular patient.

For all potential participants, a screening visit will be arranged either at the patient’s home, the Clinical Research Facility, Leazes Wing, Royal Victoria Infirmary (RVI) or at Bensham Hospital, Gateshead. The central study team (for those patients reviewed at Bensham Hospital or at home) or site-specific research staff (for those patients reviewed at the Clinical Research Facility, RVI) will discuss the study in detail with the patient and answer any queries he/she may have. If the patient wishes to take part in the study, written informed consent will be obtained at this visit.

The eligibility assessments must occur within 3 months prior to the baseline visit and the start of participation in the study. Screening logs will be held securely at the PICs and investigator sites. The screening logs will document details of patients invited to participate in the study.

#### Intervention

Lower dose LT4 achieving a target TSH level of 4.1 to 8.0 mU/L

#### Control

Standard dose LT4 achieving a target TSH level of 0.4 to 4.0 mU/L

#### Randomization

Participants will be randomized to either the usual (current) dose of LT4 (control) or the lower dose of LT4 (intervention), in a ratio of 1:1, using random permuted blocks. Randomization will be stratified by usual (pre-study) LT4 dose (50, 75, 100 and 125 mcg daily). Randomization will be administered centrally via Newcastle Clinical Trials Unit using a secure password-protected web-based system.

#### Blinding

Patients will be blind to treatment allocation. The clinicians will be aware of the LT4 dose so that they can maintain treatment within the specified TSH ranges, either for the usual dose of LT4 (control) or the lower dose of LT4 (intervention), that is, the trial will be single blinded. The research team will be aware of the dose each participant will receive; however, data analysis will be blinded.

At the final visit, the integrity of the blinding will be assessed by asking the participants if they thought they were taking their usual or a lower dose of LT4.

#### Study medication

The LT4 medication, the IMP, will be used within the licensed indications [18] in this study. Nonetheless, since an alternative dosing regime will be tested, additional information is being gathered on safety and efficacy. As manufacture will involve de-blistering/over-encapsulation, the study drug will be treated as an IMP for the purpose of this study, and will be labeled and handled accordingly.

The study drug will be sourced, assembled and packaged by Newcastle Specials (Pharmacy Production Unit) at the Newcastle upon Tyne Hospitals NHS Foundation Trust, MIA(IMP) 17136. The brand of LT4 to be used in this study will be Eltroxin 25 mcg tablets and Eltroxin 50 mcg tablets (Mercury Pharmaceutical Ltd). This will be purchased in blister packs.

The single blind will be achieved by de-blistering and over-encapsulation, using a capsule filler of lactose BP. For doses that are multiples of 50 mcg, we will over-encapsulate Eltroxin 50 mcg tablets; for the remaining 25 mcg, 75 mcg and 125 mcg dose increments, we will over-encapsulate Eltroxin 25 mcg tablets. This ensures the capsules are kept as small as possible for ease of swallowing (DB capsules size A, color: Swedish orange; manufacturer: Capsugel). Capsules will be repackaged into a bottle container (polypropylene) and labeled appropriately.

As it is not feasible to predict in advance exactly how much IMP must be packaged per study dose, predictions will be based on known current doses as per routine clinical practice; production run(s) will generate surplus stock per IMP dose.

The LT4 medication (Eltroxin 25 mcg and 50 mcg) will have a maximum shelf-life of 24 months (less any reduction in expiry due to the shortest expiry date of the blister packs purchased). The IMP will not be stored above 25 °C and will be stored in the original container to protect it from light and moisture, as per the clinical trial label. A temperature log will be maintained as per local pharmacy procedures, and appropriate IMP storage will be guaranteed until the IMP arrives in the patient’s possession.

The side-effect profile of Eltroxin (25 mcg and 50 mcg) is well known and documented [18]. The total daily dose provided to each participant will be between 25 mcg and 150 mcg.

#### Administration of study medication

Participants randomized to the lower dose of LT4 (intervention) to achieve the desired target TSH level of 4.1 to 8.0 mU/L, are likely to have their LT4 medication reduced by 25 mcg once a day at visit 1.

LT4 will be provided as two separate 13-week supplies (dispensed separately at visits 1 and 2; see Table 1). The container will be labeled appropriately but will not indicate the arm of the study to which the participants have been randomized. The label will instead contain a pack number, which will be the link to the relevant packaged dose.

**Table 1 T1:** SORTED A study assessments

	**Pre-screening**	**Screening**	**Baseline**	**Follow-up**		
**Visit**			**1**	**2**	**3**	**4 (phone call only)**
**Assessments**^**a**^	**Within 3 months of baseline visit**	**Week −4 to −1**	**Day 0**	**Week 12 (+/− 7 days)**	**Week 24 (+/− 7 days)**	**Week 25 (+/− 3 days)**
Identification and initial approach (including provision of PIS)	X					
Eligibility criteria checked (as per routine clinical practice)	X					
Written informed consent (including discussion of study in detail, questions answered)		X				
Physical examination (height,^e^ weight, blood pressure, pulse)			X		X	
Venepuncture			X^b^	X^c^	X^d^	
Clinical history (relevant medical history, medication list/history)			X			
Participant-completed questionnaires (ThyDQoL, ThySRQ, EQ-5D)			X		X	
Nurse-administered questionnaires (FRAT, TUG)			X		X	
Randomization (after all eligibility criteria checked and written informed consent obtained)			X			
Study medication prescribed and dispensed (following LT4 dose assessment at visit 2 only)			X	X		
Study medication compliance checks				X	X	
Concomitant medication			X	X	X	
Adverse events				X	X	
Serious adverse events				X	X	X

^a^ Study-specific procedures must only be performed once written informed consent is obtained from the participant; ^b^ 10 ml blood: TSH, FT4, FT3, thyroid peroxidase antibodies, total cholesterol, HDL, triglycerides, serum CTX; ^c^ 5 ml blood: TSH, FT4, FT3 only; ^d^ 10 ml blood: TSH, FT4, FT3, total cholesterol, HDL, triglycerides, serum CTX; ^e^ height to be measured at the baseline visit only.

FT3: free triiodothyronine (thyroid hormone); FT4: free thyroxine; HDL: high-density lipoprotein; serum CTX: serum collagen type-1 cross-linked C-telopeptide; TSH: thyroid stimulating hormone, PIS: participant information sheet.

The study medication will be prescribed by an authorized study physician according to the protocol, using a trial specific prescription (documenting the required IMP dose), and dispensed according to local pharmacy practice. The relevant pharmacy will hold a corresponding list allowing pharmacy staff to correlate IMP pack number with the relevant packaged IMP dose for any particular IMP bottle, thus maintaining the single blind.

To further maintain the single blind, the research team at each site will deliver the trial prescription to the pharmacy and collect the relevant study medication to provide to the patient. Participants will be advised to take the IMP capsule orally once a day as usual. This will be discussed at the time of consent and will be clear in the patient information sheet.

Participants will be informed of potential adverse reactions and advised to contact the relevant study team as required. A study-specific participant contact card will also be provided.

Once randomized, participants will begin their study medication on Day 0 (Table 1).

At 12 weeks (+/− 7 days), serum TSH levels will be checked and the LT4 dose adjusted as follows (the second bottle of IMP should be started at week 12 (+/− 7 days)):

Control (usual) dose arm, TSH level:

≤0.39 mU/L: LT4 reduced by 25 mcg once daily

0.4 to 4.0 mU/L: Stay on current dose of LT4

≥4.1 mU/L: LT4 increased by 25 mcg once daily

Lower dose arm, TSH level:

<0.4 to 4.0 mU/L: LT4 reduced by 25 mcg once daily

4.1 to 8.0 mU/L: Stay on current dose of LT4

>8.1 mU/L: LT4 increased by 25 mcg once daily

The LT4 treatment based on the above regimen will continue for a total of 24 weeks at which point the final set of study-specific assessments will be made (with a further follow-up phone call at 25 weeks). If, during the course of the study, individuals on 25 mcg/day of LT4 require a reduction in their dose of LT4, their LT4 dose will remain unchanged as otherwise they would need to discontinue LT4 therapy completely.

At visit 3, participants on each arm of the study will stop their IMP and will be referred back to their GP, who will promptly prescribe the LT4 dose they were taking prior to study participation. The GP letter (sent once the participant is randomized) and the GP follow-up letter (sent after each participant completes his/her IMP) instruct the GP to check TSH levels for each participant, three months after he/she has completed his/her IMP.

At the end of visits 2 and 3, participants will be asked to return any surplus study drug in the original packaging to the study team, who will verify and document compliance. All unused study medication and packaging will be sent to the local pharmacy for documentation and destruction as per local policy (following appropriate reconciliation by the trial manager).

Documentation of prescribing, dispensing and return of study medication will be maintained for study records.

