#### Pharmacovigilance

The safety of the lower dose of LT4 in this study will be evaluated by examining the occurrences of all adverse events, adverse drug reactions, unexpected adverse reactions, serious adverse reactions or suspected unexpected serious adverse reactions as defined by the Medicines for Human Use (Clinical Trials) Regulations [19]. The relationship and expectedness of the adverse event or reaction (causality) will be assessed by the site investigator and relayed to the chief investigator who, on behalf of the sponsor (Newcastle upon Tyne Hospitals NHS Foundation Trust), will notify the regulatory bodies, the Medicines and the Healthcare Products Regulatory Agency (MHRA) and the research ethics committee (REC), within 7 days for fatal and life-threatening events and 15 days for non-life-threatening events. All study investigators will be notified.

Most adverse events and adverse drug reactions that occur in this study, whether they are serious or not, will be expected treatment-related toxicities due to the drugs used in this study. A full summary of product characteristics of Eltroxin have been published [18].

We do not anticipate adverse effects for the lower dose of LT4. Although the current uniform serum TSH reference range of 0.4 to 4.0 is applied across all age groups, in real practice a significant proportion of individuals do have biochemical features of mild under-replacement, which goes unrecognized until a blood test is performed. If severe hypothyroidism develops (TSH >10 mU/L with low FT4 levels), then symptoms including fatigue, weight gain and poor memory may develop. We will assess the clinical impact of thyroid function via hypothyroid-specific symptom checklists, ThySRQ, and biochemically (TSH and FT4 levels) at 12 and 24 weeks to detect individuals who are unwittingly developing severe hypothyroidism. We will adjust their LT4 dose accordingly. Participants will also be provided with a helpline number in case they experience any problems.

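### The exit rule returns every participant to the pre-study LT4 dose with no TSH condition, so a control retitrated at week 12 goes back to the dose on which TSH was out of range

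*Protocol article*

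**What the plan says.** All references are to the Protocol article, SORTED A.

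- **Dose at entry.** The Randomization section allocates controls to their usual dose and stratifies by that dose (50, 75, 100 or 125 mcg daily). Under Inclusion criteria, entry requires: "All of their TSH results are within the range 0.4 to 4 mU/L in the 3 months before commencing the study".
- **Week 12, control arm.** Administration of study medication gives the rules "≤0.39 mU/L: LT4 reduced by 25 mcg once daily" and "≥4.1 mU/L: LT4 increased by 25 mcg once daily". Between these limits the dose stays as it is.
- **Exit.** The same section stops study drug at visit 3 in both arms. Participants are "referred back to their GP, who will promptly prescribe the LT4 dose they were taking prior to study participation". Two GP letters, one after randomization and one after study drug ends, ask the GP "to check TSH levels for each participant, three months after he/she has completed his/her IMP".
- **Safety review.** Pharmacovigilance says that symptoms, TSH and FT4 will be assessed "at 12 and 24 weeks to detect individuals who are unwittingly developing severe hypothyroidism" and adds: "We will adjust their LT4 dose accordingly". It defines severe as TSH above 10 mU/L with low FT4.
- **Timing.** Table 1 puts visit 3 at week 24 with a window of 7 days either side, and the closing phone call at week 25 with a window of 3 days either side. The call records serious adverse events only.

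**The concern.** The titration rule and the exit rule pull against each other. At week 12 the protocol treats a control's out-of-range TSH as sufficient reason to change the dose. Twelve weeks later it undoes that change for everyone, even where the week-24 TSH shows that the new dose brought the participant into range.

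The consequence is a safety matter and does not bias any estimate. The Background section lists atrial fibrillation and cardiovascular mortality among the potential harms of over-treatment, and every participant is aged 80 or over. A control cut for a suppressed TSH would resume the higher dose for about three months before the next planned measurement. The Blinding section says that the clinicians know the dose, so someone in the trial is in a position to give better advice. SORTED is also meant to test procedures for SORTED II, so an exit rule left as it is could carry into the larger trial.

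**Working it through.** **1. Control dose path.** The inputs are the four strata (Randomization), the 25 mcg week-12 step and the return to the pre-study dose (Administration of study medication). The change at exit is 25 divided by the dose held from week 12 to week 24.

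| Pre-study dose (mcg) | After a cut, then exit | Change at exit | After a rise, then exit | Change at exit |
|---|---|---|---|---|
| 50 | 25, then 50 | 25/25 = +100% | 75, then 50 | 25/75 = -33% |
| 75 | 50, then 75 | 25/50 = +50% | 100, then 75 | 25/100 = -25% |
| 100 | 75, then 100 | 25/75 = +33% | 125, then 100 | 25/125 = -20% |
| 125 | 100, then 125 | 25/100 = +25% | 150, then 125 | 25/150 = -17% |

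In every stratum the retitrated control ends on the dose at which the out-of-range value was measured. The step is always 25 mcg. The larger percentages reflect the smaller doses.

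**2. How many controls.** The target of 50 at 1:1 gives 25 controls. The protocol gives no figure for the share p out of range at week 12, so p is an assumption. The expected number is 25p, and the chance of at least one is 1 - (1 - p)^25.

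| Assumed p | Expected controls | Chance of at least one |
|---|---|---|
| 2% | 0.5 | 40% |
| 5% | 1.25 | 72% |
| 10% | 2.5 | 93% |
| 20% | 5 | >99% |

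These count both directions. Controls cut for low TSH are only part of them.

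**3. Exit change from the week-24 dose, all paths (mcg).**
- Control: unchanged 0; cut at week 12 +25; raised at week 12 -25.
- Lower dose (taking a 25 mcg cut at visit 1): unchanged at week 12 +25; cut again +50 (+25 if already at the 25 mcg floor); raised 0.

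In 3 of these 6 paths the preset return gives no rise. This counts paths, not patients. It matters only if the week-24 result shows severe hypothyroidism.

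**4. Call window.** Visit 3 is day 168 ± 7, or days 161 to 175. The call is day 175 ± 3, or days 172 to 178. The gap from visit 3 to the call runs from 172 - 175 = -3 to 178 - 161 = +17 days. Of the 15 × 7 = 105 allowed day pairs, 6 put the call before visit 3, 4 on the same day, and 49 at 4 to 10 days after. This counts allowed combinations and is not a forecast.

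**The case against.** The pre-study dose is a defensible default. Every participant had to have TSH in range at entry. The contrary evidence for a retitrated control is one week-12 reading, taken on over-encapsulated Eltroxin that may not match the usual product. The three-month GP check is about as long as the trial's own 12-week interval between measurements. A control raised for TSH of 4.1 or above and then returned may well sit in the range that the trial targets in its other arm, so the named over-treatment harm does not apply. All of this stands. It limits the point mainly to controls cut for low TSH and to a limited exposure. It does not explain why a dose change that the protocol itself required should be reversed without anyone looking at the result.

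Three stronger readings are tempting, and the documents do not support them:

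- **That the exit rule contradicts Pharmacovigilance.** Study drug stops at visit 3, so a promise to adjust the dose on a week-24 result can only concern what follows. It can fairly be read as an exception to the default. How it would work is not described, but that is a gap in mechanism and not a contradiction.
- **That the trial ignores week-24 results it already holds.** Table 1 draws that blood at visit 3, the visit at which study drug stops. The result cannot be assumed to be available then, and prompt resumption of a known dose avoids a gap in treatment. The week-12 result and the dose change are in hand.
- **That serious adverse events after the switch will be missed.** The call is numbered after visit 3 and described as a further follow-up, so the intended order is clear. An overlap needs a late visit and an early call, and staff can avoid it. Participants also have a contact card and a helpline.

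The article does not reproduce the full GP letters. They may already carry results or dose advice.

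**Conclusion.** The point holds in a limited form. As written, the exit rule overrides the trial's own week-12 titration in the control arm and returns those participants, by one 25 mcg step, to a dose on which TSH was out of range, until the GP's three-month check. The safety concern is mainly for controls cut at TSH of 0.39 mU/L or below. For the lower-dose arm, returning to the pre-study dose is sensible, because TSH was required to be in range at entry.

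The number affected is unknown and probably small: 0.5 to 5 of 25 controls across the assumed 2% to 20%, in both directions together. The conclusion rests on a literal reading of the exit sentence and on the GP letters containing no further dose advice. The call window is a small timing defect. No outcome estimate changes. The severity is minor, but the remedy is specific and cheap.

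**What to change.** 1. **Exit rule.** Keep the pre-study dose as the default. Add that for a control whose dose was changed at week 12, the unblinded study clinician advises the GP on the exit dose. This would normally be the retitrated dose if the week-24 TSH is within 0.4 to 4.0 mU/L. A control moved from 100 to 75 mcg and then in range would stay on 75 mcg.
2. **Week-24 results.** Send TSH and FT4 with the existing GP follow-up letter. Include dose advice where the result shows severe hypothyroidism, which gives the Pharmacovigilance promise a route.
3. **Final call.** Time it from the actual visit 3 or last dose of study drug, for example 7 ± 3 days after. It would then always fall 4 to 10 days after study drug stops.

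The cost is a sentence or two in the exit rule, one column heading in Table 1, and results and advice added to a letter already sent. No visit or blood test is added. The downside is a brief clinician review of results already collected. A few participants may also have a second dose change soon after the first, because the week-24 result arrives after study drug has stopped.
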